# Efficacy of hearing aid treatment on sound perception and residual hearing preservation in patients with tinnitus and coexisting hearing loss: study protocol for a randomized controlled trial

**DOI:** 10.1186/s13063-022-07014-0

**Published:** 2022-12-27

**Keywords:** Subjective tinnitus, Sensorineural hearing loss, Hearing aids, Randomized controlled trial

## Abstract

**Background:**

Chronic subjective tinnitus poses significant challenges in clinical practice, and it is usually associated with hearing impairment, particularly with high-frequency sensorineural hearing loss (SNHL). Patients suffering from tinnitus with SNHL experience one of the most severe sensory disabilities, and this has devastating effects on their quality of life. Nowadays, mild to moderate SNHL can be managed with a properly fitted hearing aid (HA) that provides sound amplification, and several studies suggest that HAs may also benefit those with tinnitus. However, inadequate attention has been paid by medical personnel to the impact of HA use in residual hearing protection for patients with tinnitus and coexisting SNHL, and existing evidence is still at a preliminary stage. This study aims to identify and evaluate the efficacy of the use of HAs in both sound perception and residual hearing preservation among patients with tinnitus and coexisting SNHL.

**Methods and design:**

The present study is a prospective, single-center, outcome assessor and data analyst-blinded, randomized, controlled trial. Eligible participants will be recruited and randomly allocated into the HA intervention group and the waiting list control group at a ratio of 1:1. The primary outcome is to evaluate the severity of tinnitus using the Tinnitus Handicap Inventory as a continuous variable at 6 months from randomization. Secondary outcome measures include changes in hearing status and mental states. The trial will last 6 months, with follow-up visits at 3 months and 6 months.

**Discussion:**

This will be the first randomized, controlled trial to identify and evaluate HAs’ efficacy on residual hearing preservation among tinnitus patients with coexisting high-frequency SNHL in China. We are aiming for novelty and generalizability, and strengths of this study are that it will examine the effectiveness of HA in patients with tinnitus and hearing impairment and will further explore the residual hearing protection provided by HA treatment in the tinnitus group.

**Trial registration:**

ClinicalTrials.gov NCT05343026. Registered on April 25, 2022

**Supplementary Information:**

The online version contains supplementary material available at 10.1186/s13063-022-07014-0.

## Background

Subjective tinnitus is defined as an auditory perception without a corresponding auditory stimulus [1], and it has attracted considerable critical attention as a distressing and debilitating audiological condition in clinical practice. Tinnitus increases steadily with age, and the recently reported prevalence of tinnitus is approximately 10 in 100 adults [2, 3], but this is likely to be an underestimation due to poor awareness of the need for timely medical treatment in some patients. Tinnitus can be divided into acute or chronic tinnitus according to its duration. Of particular concern is that about 45 to 78% of patients with chronic tinnitus report bothersome irritability, anxiety, depression, insomnia, and deterioration of social function [4–7]. Current methods for tinnitus management involve cognitive behavioral therapy (CBT), sound therapy, and educational counseling [8]. For most tinnitus cases, the pathophysiological causes are still in dispute [5], so previous specific tinnitus treatments remain substantially heterogeneous [1]. Accordingly, there is an urgent need to develop an effective management strategy for tinnitus.

Moreover, most patients with chronic subjective tinnitus are comorbid with high-frequency sensorineural hearing loss (SNHL) [9]. The occurrence of tinnitus with SNHL presents one of the most common sensory disabilities, leading to a deleterious impact on patients worldwide. It has been recently argued that the generation and maintenance of most tinnitus cases are strongly linked to acquired hearing impairment, especially when the SNHL is associated with distinct neuronal changes in auditory and extra-auditory brain networks [10]. Presbycusis is a mostly irreversible phenomenon that results from the progressive deterioration of hair cell function in the inner ear [11]. With the increased aging of the population, it is predicted that the incidence rate of this condition will continue to increase. However, no strategies are currently available in clinical practice to reverse the progression of this disorder.

Currently, the use of hearing aids (HAs) is widely considered to be an effective instrument for older patients with hearing disabilities. HAs mostly function through sound amplification, and it is noteworthy that the enhanced performance of receiving acoustic information by using HAs is also seen in patients with significant residual hearing [12]. Surprisingly, several studies have shown that HAs might help patients cope with their tinnitus by increasing the external volume to help cover the tinnitus sound [13–16]. However, these previous studies in general do not comprehensively explore the role of HA in the severity or loudness of tinnitus, and there is still little agreement on the relationships between the HA intervention and residual hearing preservation in terms of hearing improvement.

Considering the lack of compelling evidence regarding the extent to which HAs play a role in sound perception and residual hearing preservation among patients with tinnitus and coexisting SNHL, we designed this single-blind, 6-month, randomized, controlled trial with two parallel groups. The first is the HA treatment group, and the second is the waiting list control (WLC) group that will receive non-HA interventions during the study period. We hypothesize that the HA intervention will improve tinnitus patients’ quality of life in terms of improvements in the speech recognition score (SRS), the Tinnitus Handicap Inventory (THI), the Hospital Anxiety and Depression Scale (HADS), and the Athens Insomnia Scale-8 (AIS-8) without affecting residual hearing.

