## Methods/design

### Study design and settings

The study protocol will follow the *2013 Standard Protocol Items: Recommendations for Interventional Trials (SPIRIT) Statement* [17] (Additional file 1). This study is a prospective, single-center, outcome assessor and data analyst-blinded, randomized, controlled trial with superiority test in the framework lasting 6 months with an allocation ratio of 1:1 for the intervention and WLC groups. Patients will be recruited from the tinnitus outpatient clinics of the Eye and ENT Hospital of Fudan University in Shanghai, and the trial will be conducted by qualified and well-trained doctors, investigators, and HA technicians using appropriate experimental facilities.

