In addition, a large population of tinnitus patients who suffer from related psychological distress seems to have negative emotional performance [44]. So far, there has been little agreement on how best to manage the mental status of tinnitus patients. The most widely recognized strategy focusing on neuropsychiatric complications is CBT. However, to date, research has not determined whether CBT improves tinnitus’s perceptual characteristics or improves the general quality of life by changing the awareness of tinnitus [41]. Moreover, CBT is ineffective for patients with combined SNHL. Another potential problem with CBT is that it is a time and energy-consuming therapy and requires substantial support from psychiatrists, psychologists, and family connections. HAs, in contrast, are simple, safe, and easy to use, and prior studies have noted the importance of HA use in mental status management in tinnitus patients [14, 42]. To the best of our knowledge, there is no evidence supporting a link between HA treatment and the preservation of residual hearing, and more detailed RCT studies are still required to compensate for the shortcomings of previous studies [16], as well as to further determine the efficacy of HAs in patients suffering from tinnitus with coexisting SNHL.

The present study, which differs from other trials, seeks to comprehensively prove that HAs are effective in patients with tinnitus and hearing impairment and to further explore the residual hearing protection by HA treatment in the intervention group. The strengths of the study rest on several aspects. For instance, we designed the HA treatment as a stand-alone intervention with clearly defined inclusion criteria, including the subjective tinnitus duration and specific PTA thresholds per frequency. Thus, it will be possible to avoid combining the study with other tinnitus treatments and avoid selection bias, which will improve the reliability and credibility of the observation results. Additionally, patients will be recruited from an ENT-specialized hospital, where adequate eligible participants can be obtained. Moreover, the study findings might contribute to profound advances in tinnitus treatments and may serve as a helpful reference for other countries. When the efficacy of the HA can be verified, it may have positive implications in the clinical setting as to its role in alleviating tinnitus and preventing the coexisting SNHL from deteriorating.

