This study is not exempt from limitations. For example, most self-report questionnaires are subjective and are prone to reporting bias due to participants’ non-adherence and vague memory. Participants have to be encouraged to answer truthfully, and to some extent, the outcomes provided by caregivers can be added as complementary information. Also, the use of WLC groups has been regarded as an ethical alternative to control groups, but this can potentially pose problems. As a solution to the limitation that participants in the WLC group are stalled at the stage of change regarding readiness, we set the enrollment to be mild and acceptable symptoms, and we will provide periodic health advice to all participants. Another point worth mentioning is that cochlear implant (CI) technology currently effectively restores hearing by stimulating the cochlear nerve [44, 45]. However, although CIs are capable of protecting residual hearing, they are invasive and are prohibitively expensive. Accordingly, early benefits from HA use can be expected in patients with residual hearing. Nevertheless, if the effectiveness is less pronounced with HAs, the use of CIs may be necessary.

To conclude, this will be the first randomized controlled trial to evaluate the efficacy of HAs on sound perception and residual hearing preservation among tinnitus patients with SNHL in China. Despite its limitations, this study is unique and will contribute to knowledge about HAs’ roles in residual hearing preservation in these patients. The results from this trial are expected to provide support for doctors to provide more effective advice in clinical practice.

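### The hypothesis that hearing aids leave residual hearing unaffected is a no-worsening statement, and the superiority framework the protocol states cannot support it

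*Protocol article*

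**What the plan says.** The Background hypothesis lists gains in speech recognition, THI, HADS and AIS-8 and closes with a condition on hearing ("AIS-8) without affecting residual hearing"). The abstract's aim gives hearing equal billing: the "efficacy of the use of HAs in both sound perception and residual hearing preservation among patients with tinnitus and coexisting SNHL". The conclusion of the Discussion repeats that the trial will "evaluate the efficacy of HAs on sound perception and residual hearing preservation among tinnitus patients with SNHL".

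Under Study design and settings the trial is described as a "randomized, controlled trial with superiority test in the framework lasting 6 months". No other testing framework is named. The abstract places hearing among the secondary outcomes: "Secondary outcome measures include changes in hearing status and mental states".

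The statistical methods section names a *t*-test for the THI, HADS and AIS scores. It adds a linear model with age, gender and baseline value as covariates and, if applicable, a mixed model. Adjusted effect estimates and their 95% confidence intervals are given one stated purpose, to determine statistical significance. The sample size rests on a comparison of two THI proportions.

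The Discussion also says the trial seeks "to further explore the residual hearing protection by HA treatment in the intervention group". The same section hopes that hearing aids may keep the coexisting hearing loss from getting worse.

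**The concern.** A superiority test can reject equality; it cannot establish it. A hypothesis that hearing is not affected needs a stated size of worsening that the data must rule out. The framework as written gives a test of difference and a significance reading of the interval, so one half of the stated hypothesis cannot be confirmed by the stated analysis.

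The article also gives residual hearing two meanings. In the hypothesis it is not harmed. In the Discussion it is protected from decline. The first needs a margin, the second needs superiority over the waiting list. If the two are not separated, a null PTA result could be reported under the first meaning and a favourable one under the second. Hearing is formally secondary, but preservation is in the title, the aim and the conclusion, so readers are likely to carry this claim away.

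**Working it through.** **Plan's own figure.** No sample size, SD or margin is given for PTA, so there is no PTA figure to reproduce. The only calculation is for THI response: 56 participants, i.e. 56/2 = 28 per arm, raised to 31 for 10% loss (28 × 1.1 = 30.8). The comparator proportion is not stated, so 56 cannot be re-derived, and this point does not depend on it.

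**Inputs.**
- n = 28 per arm with data at 6 months (sample size section).
- α = 0.05 (same section; two-sided is assumed, as sidedness is not stated).
- SD of PTA change: not in the documents. Assumed values of 3 to 10 dB are shown, with 5 to 7 dB as the working range.
- 3 dB and 5 dB are illustrative sizes, not values from the documents.

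**Formulas.**
- SE = SD × √(2/28).
- 95% CI half-width = t(0.975, 54 df) × SE = 2.005 × SE.
- Probability that a true worsening d is non-significant = P(|T| < 2.005), where T is non-central t with 54 df and non-centrality d/SE.
- Probability that the CI excludes a worsening of 5 dB when the true difference is 0 = P(T > 2.005) with non-centrality 5/SE.

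**Numbers for SD 5.** SE = 5 × √(2/28) = 1.336 and the half-width is 2.005 × 1.336 = 2.68. For d = 3 the non-centrality is 3/1.336 = 2.25, and the test misses 40%. For d = 5 it is 5/1.336 = 3.74, and the test misses 4%.

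**Numbers for SD 7.** SE = 1.871 and the half-width is 3.75. For d = 3 the non-centrality is 1.60, and the test misses 65%. For d = 5 it is 2.67, and the test misses 25%.

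| Assumed SD (dB) | SE | 95% CI half-width | True 3 dB worsening non-significant | True 5 dB worsening non-significant | CI excludes 5 dB if true difference is 0 |
|---|---|---|---|---|---|
| 3 | 0.80 | 1.61 | 4% | 0% | 100% |
| 5 | 1.34 | 2.68 | 40% | 4% | 96% |
| 7 | 1.87 | 3.75 | 65% | 25% | 75% |
| 8 | 2.14 | 4.29 | 72% | 37% | 63% |
| 10 | 2.67 | 5.36 | 80% | 55% | 45% |

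A normal approximation gives miss probabilities up to 2 points lower. With all 31 per arm retained, the half-widths at SD 5 and 7 are 2.54 and 3.56 dB.

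**Reading.** Unless the SD is small, a non-significant result is compatible with a 3 dB worsening. The same interval, held against a margin, answers the no-worsening question directly. How well it does so depends on the SD. For an illustrative 5 dB margin at 80% power and one-sided 0.025, the need is about 16 per arm at SD 5, but 41 at SD 8 and 63 at SD 10, against 28 available.

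**The case against.** Several points on the other side are fair.

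- *Hearing is secondary, and the superiority label may be meant for the THI comparison.* A margin for a secondary outcome could also sit in an analysis plan that is not shown. So the absence of a margin is not in itself the fault. What stands is the conflict within the article: a no-worsening hypothesis beside a single stated framework that cannot support it.
- *A baseline-adjusted interval is already planned.* The statistical methods do plan adjusted estimates with 95% intervals, so the needed quantity will broadly exist. But its stated use is to decide significance, not to rule out harm of a given size.
- *Preservation need not mean no worsening.* A reader might infer that the whole title question is a no-worsening claim. The documents do not support that. The Discussion's sense of preventing deterioration can be tested by superiority over the waiting list. Only the closing clause of the hypothesis is a no-effect statement.
- *No decision rule says that non-significance means preservation.* A reader might infer one, but no section states it. The point is that the stated framework offers no valid route to the claim.
- *A within-group analysis is not planned.* The phrase "to further explore the residual hearing protection by HA treatment in the intervention group" might suggest one. It may simply name who receives the device, and under Time points both groups have PTA, speech and DPOAE follow-up.
- *The test is not blind to harm.* A reader might infer that the PTA comparison would be null whatever the truth. At SD 5 a true 5 dB worsening would be detected with 96% power. The weakness concerns smaller differences or larger SDs.

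**Conclusion.** The concern holds in a limited form. The hypothesis that hearing is unaffected cannot be supported by the superiority framework and the significance-based use of intervals that the article states, and the article uses a second, superiority-type meaning without separating the two. With 28 per arm and an assumed SD of PTA change of 5 to 7 dB, a two-sided test at 0.05 would miss a true 3 dB worsening about 40 to 65% of the time and a true 5 dB worsening about 4 to 25% of the time. A non-significant difference would therefore not show that hearing is unaffected. These sizes rest on the assumed SDs and on an unadjusted two-sample comparison; baseline adjustment may change the effective SD. The conflict in wording does not depend on any of these numbers. It should be corrected, but it concerns a secondary outcome and leaves the primary THI comparison untouched.

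**What to change.** Separate the two readings in the protocol.

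- *Not affected.* Judge the between-group, baseline-adjusted difference in 6-month PTA by its 95% CI against a margin that the sponsor pre-specifies and justifies. Conclude that hearing is preserved only if the CI excludes a worsening of that size.
- *Protection.* Claim it only if the hearing aid group is shown superior to the waiting list group.
- *Neither adopted.* Label the hearing results descriptive, and state that no preservation conclusion will be drawn from a non-significant test.

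State which PTA measure carries the claim, because the article uses 2–8 kHz for eligibility and lists 0.5, 1, 2 and 4 kHz for testing.

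The cost is a few sentences and agreement on a margin before the data are seen; no new measurements are needed. The downside is that if the SD turns out near 8 to 10 dB, the half-width of 4.3 to 5.4 dB may be too wide to support a margin near 5 dB. The result must then be reported as inconclusive.

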## Methods/design

### Study design and settings

The study protocol will follow the *2013 Standard Protocol Items: Recommendations for Interventional Trials (SPIRIT) Statement* [17] (Additional file 1). This study is a prospective, single-center, outcome assessor and data analyst-blinded, randomized, controlled trial with superiority test in the framework lasting 6 months with an allocation ratio of 1:1 for the intervention and WLC groups. Patients will be recruited from the tinnitus outpatient clinics of the Eye and ENT Hospital of Fudan University in Shanghai, and the trial will be conducted by qualified and well-trained doctors, investigators, and HA technicians using appropriate experimental facilities.

### Participants

Eligible patients who fulfill all of the following criteria will be recruited:Adults aged older than 18 years old and less than 70 yearsChronic (> 6 months) subjective tinnitus, unilateral or bilateralDiagnosed with mild high-frequency SNHL (pure tone audiometry (PTA) average of 25–40 dB at 2–8 kHz)Available for 6 months after starting the study to complete the follow-up questionnairesReadiness to participate in the study and sign the informed consentBe covered by public health insurance and be eligible for reimbursement

Patients with any of the following exclusion conditions will not be enrolled:Objective tinnitusConductive HLUnstable medical history that limits participationUndergoing any other research clinical studiesHaving used HAs in the past yearUnwilling or unable to use HAs dailyAlcohol or drug abuse

### Recruitments and randomization

This study will be conducted in the outpatient ENT department of the Eye and ENT Hospital of Fudan University in Shanghai, China. Our institution is a specialized hospital focused on otorhinolaryngology. In addition, we developed an app—the Fudan Tinnitus Relieving System (FTRS)—that will be used for the management, treatment, data collection, and efficacy analysis of tinnitus patients. The participants will be primarily included in the study after being diagnosed with probable chronic subjective tinnitus with bothersome symptoms after the screening procedure. Screening for hearing and tinnitus testing typically consists of PTA, speech audiometry test, and distortion product otoacoustic emissions (DPOAE) along with several widely accepted tinnitus questionnaires such as the THI for tinnitus severity, the visual analog scale (VAS) for tinnitus loudness, and the HADS and AIS-8 for mental health status. The entire test will generally take a mean time of approximately 30 min. Participants will scan the two-dimensional code we supply via their smartphones and will fill out the questionnaires online through the FTRS.

Interested patients will be directed to the research room to receive the necessary details of the study. Before participation, informed and written consent will be obtained from all participants by the principal investigator. The randomization will be stratified by the THI score (≤ 36 or > 36 [18]) based on the baseline assessment in order to avoid an uneven distribution of patients. An independent researcher who is not involved in the recruitment process or outcome measurement will generate a random sequence (http://www.random.org) to randomly assign the participants in a 1:1 allocation to treatment using HAs or to the WLC group. The randomization sequence will be concealed in sequentially numbered sealed and opaque envelopes. Participants will then be notified via telephone or email which group they are allocated to by the staff member who kept the randomization sequence file and who will not participate in any subsequent assessment of the patients. Data analysts, study coordinators, and outcome assessors will remain unaware of the group assignments until the primary analyses are completed.

### Intervention

Following randomization, the participants will be immediately invited to provide personal information including primary demographic data and clinical characteristics. Demographic variables will include gender, age, occupation, residential address, education level, date of onset, and comorbidities. Once participants are randomized and the baseline measurements are complete, the intervention will begin.

Participants in the treatment group are required to wear the HAs for at least 3 h per day and for at least 24 days per month. The HAs will be fitted unilaterally or bilaterally on the side affected by tinnitus, and the HA fitting prescription will be in accordance with the NAL-NL1 procedure [19]. A comfortable and precise level of auditory perception is of the utmost importance in the debugging process of the HA. We will also evaluate the HA performance in the HA treatment group using the Abbreviated Profile of Hearing Aid Benefit (APHAB) questionnaire. The non-HA treatment group is a WLC in which participants will receive the intervention after the waiting period has passed. All participants will receive regular counseling and lifestyle education from physicians during the study period.

The flow chart for participant visits and follow-ups is shown in Fig. 1. To assess the outcome efficacy of HAs, all of the participants will undergo follow-up assessments at 3 months and 6 months after the start of the intervention.

